### Secondary outcomes

Secondary outcome data will also be collected at the 12 month follow-up appointment including:number of new foot ulcers;time to onset of new foot ulcer(s);new lower extremity amputation(s) (including level of amputation and reason for amputation);episodes of infection of the foot or lower extremity (including type of infection);episodes of osteomyelitis;foot-related hospitalisations (including reason for admission, length of stay and foot-related treatments/procedures received during hospital admission);revascularisation procedure(s) of the lower extremity (including type of procedure);new podiatry interventions (e.g. nail reduction, prescription of foot orthoses);kidney transplantation and;mortality (including primary and secondary causes of death).

All secondary outcomes will be self-reported by participants and then verified by reviewing medical records. All medical histories of participants will be reviewed to determine whether any of the secondary outcomes occurred during the 12-month follow-up period. The time to onset of new foot ulcer(s) will be defined as the ‘number of days between the baseline appointment and the development of a new foot ulcer’. Medical records will be referred to for the first documented encounter of the new foot ulcer and this date will be recorded. A lower extremity amputation will be defined as a ‘complete loss of any part of the lower extremity [74], including any digit, partial foot amputation or higher’. Lower extremity amputations resulting from accidental trauma unrelated to ESRD or the presence of a tumour will not be recorded. Lower extremity amputations will be classified as major or minor. A major amputation will be documented if there is loss of limb above the ankle, or minor amputation if below the ankle [74, 75]. Mortality data will also be collected at the follow-up appointment. Date of death (including primary and secondary causes of death) will also be recorded from reviewing patient medical histories. For those participants that die during the study period, hospital medical records will be reviewed to assess for the primary and secondary outcomes up until the date of death.

### Sample size

Prospective sample size calculations were performed using Stata 11 Data Analysis and Statistical Software (StataCorp LP, Texas, USA) for the following predictor variables; diabetes mellitus and peripheral neuropathy. Based on these calculations, a sample of 430 participants will provide 80 % power to detect a clinically worthwhile difference of 15 % in the incidence of foot ulceration between those with and without diabetes. This sample size will also provide 80 % power to detect a clinically worthwhile difference of 10 % in the incidence of foot ulceration between those with and without peripheral neuropathy. This sample size also allows for a 20 % loss to follow-up.

### Data handling and statistical analysis

Data will be entered into a Microsoft Excel® spread sheet for the development of an analytical file. A predefined statistical analysis plan will be established between an experienced biostatistician ([name]) and the research team prior to commencing the analysis. Baseline sociodemographic, health-related quality of life and clinical characteristics of participants will be calculated and expressed as mean ± standard deviation or median (25^th^ to 75^th^ percentile) for continuous variables and number (proportion) for categorical variables. For comparison of baseline variables between different groups (for example, foot ulcer or no foot ulcer), independent samples *t*-tests will be calculated for continuous variables and chi-square (*χ*^2^) tests for categorical variables. Unadjusted foot ulcer incidence rates will be calculated for number of events per 1000 person-years. Multivariate Cox proportional hazards models will be used to assess predictors of new foot ulceration and time to event secondary outcomes. Logistic regression will be used for binary outcomes, such as prevalence of foot ulcerations.

Base regression models will be developed to fit each risk factor one at a time with other variables including baseline demographics and possible confounders as described in Table 9 [9, 76, 77], and statistical significance will be assessed. As a sensitivity analysis, we will also use forward selection when building models with *P*-values set at 0.1. Confounders will be retained if they change the estimated associations between risk factors and the outcome by 10 % or more, or are significant at the 5 % level in adjusted models [78]. After a number of iterations, all risk factors will then be combined in a multivariable regression model. Possible interactions will also be assessed. Strata specific analysis of regression models using diabetes (yes/no) and sex (male/female) will be conducted to assess variables for possible effect modification. Interaction terms will then be included in the regression models if there is evidence of an effect modification from any of these variables. Risk estimates will be presented as hazard ratios and/or odds ratios (depending on the regression model) with corresponding 95 % confidence intervals (CIs). Statistical significance will be set at the conventional level of *P* < 0.05.

**Table 9 Tab9:** Risk factors and potential confounding variables

Continuous variables	Categorical variables
Participant characteristics	Participant characteristics
• **Age**	• **Male sex**
• **Body mass index**	• **Current smoker**
Health-related quality of life (SF-36v2®)	• **Living alone**
• Physical Component Score	Comorbidities
• Mental Component Score	• **Diabetes mellitus**
Comorbidities	• **Retinopathy**
• **Duration of diabetes**	• **Peripheral neuropathy**
Dialysis-related variables	• **Peripheral arterial disease**
• **Duration of dialysis**	• **Arterial calcification**
Laboratory blood tests	• **Hypertension**
• C-reactive protein	• **Dyslipidaemia**
• Serum albumin	• **Ischaemic heart disease**
• Total calcium	• **Congestive cardiac failure**
• Serum phosphate	• **Cerebrovascular disease**
• Parathyroid hormone	• Osteoarthritis
• Glycated haemoglobin (HbA1c)	• Inflammatory arthritis
• Haemoglobin	Lower extremity complications
Other	• **Previous foot ulceration**
• Peak plantar pressures	• **Current foot ulcer present at baseline**
	• **Previous lower extremity amputation**
	Other
	• Reduced range of motion of the 1^st^ metatarsophalangeal joint
	• **Foot deformity**
	• **Inappropriate/ill-fitting footwear**
	• Skin pathology
	• Nail pathology
	• Poor foot health care behaviours
	• Regular podiatry attendance

Potential confounding variables that will be considered in the regression models are boldface

Intra-examiner reliability of the assessor ([name]) will be evaluated using ICCs for continuous data and the weighted kappa (κ) statistic for ordinal data. To assess the strength of linear correlation between the two measurements (i.e. to detect random and systematic errors) [25], ICCs and corresponding 95 % CIs of the type (3, 1) will be calculated for single measures and type (3, *k*) for average measures. ICC values >0.75 indicate good reliability, ICCs ranging from 0.50 to 0.75 imply moderate reliability and ICCs <0.50 suggest poor reliability [25]. The 95 % Limits of Agreement will also be calculated to examine the level of agreement between the two measurements [25, 79]. Absolute agreement in addition to linear weighted kappa will be calculated for ordinal data to determine the proportion of the total amount of agreement between the two measurements that is not explained by chance [80, 81]. Weighted kappa values >0.8 represent excellent agreement, >0.6 substantial levels of agreement, 0.4 to 0.6 moderate agreement and <0.4 poor to fair agreement [25].

Data analysis will be undertaken using IBM SPSS version 22.0 or later (IBM Corp, Somers, NY, USA), Stata 11 Data Analysis and Statistical Software (StataCorp LP, Texas, USA), QualityMetric Health Outcomes™ Scoring Software 4.5.1 and FootMat™ 7.0 Software (Tekscan Inc, South Boston, MA, USA).

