#### Biomechanical assessment

Anomalies of foot structure have been found to be predictive of foot ulceration in prospective studies [41, 55, 56]. The grading of hallux valgus will be evaluated using the Manchester Scale [57], as it provides a valid representation of the degree of hallux valgus deformity [58]. Intra- and inter-rater reliability have been found to be excellent, with kappa (κ) values of 0.77 and 0.86, respectively [57]. Foot deformity will be recorded if any of the following are present:Hallux abducto valgus (graded in accordance with the Manchester Scale) [35, 57];Hammer/claw toes [35];Bony prominences (e.g. prominent metatarsal heads);Charcot neuroarthropathy [35];Other (e.g. forefoot pad atrophy).

Limited joint range of motion (e.g. first metatarsophalangeal joint) has also been associated with an increased risk of foot ulceration in prospective and case–control studies [55, 56, 59].

Dorsiflexion range of motion of the first metatarsophalangeal joint will be assessed in accordance with the ‘static non-weightbearing technique 1’ described by Hopson et al. [60]. This technique has been shown to be a reliable clinical measurement (ICC = 0.95). Limited range of motion at the first metatarsophalangeal joint will be documented if:Passive, non-weightbearing dorsiflexion is <65° (either foot) [60].

Elevated peak plantar pressures have been found to be a statistically significant predictor of diabetic foot ulceration in prospective studies [61–63]. Peak plantar pressures will be assessed during level barefoot walking using a two-step gait initiation protocol [64] with the Tekscan Matscan® system (Tekscan Inc, South Boston, MA, USA). Peak plantar pressures will be measured at seven regions of the foot, including the heel, midfoot, first metatarsophalangeal joint, second metatarsophalangeal joint, third to fifth metatarsophalangeal joints, hallux, and lesser toes [64]. The mean peak plantar pressure values of the three trials (of each foot) will be used for the purposes of analysis.

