## Conclusion

This is the first multi-centre prospective observational cohort study to investigate risk factors for foot ulceration in adults with ESRD treated with dialysis. In addition, we have pre-specified our sample size to ensure clinically and statistically meaningful results. The study will improve on prior studies by using prospective methods, multi-centre recruitment, statistical methods to control for confounding variables, and a pre-specified sample size estimation. The results will provide high-level evidence, and a temporal sequence of events for risk factors contributing to the development of foot ulceration in the dialysis population. The identification of potentially modifiable risk factors can inform the design of future trials investigating the effectiveness of clinical interventions to reduce the burden of lower limb disease in adults on dialysis.

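### The combined Cox model of all risk factors has no limit on terms, and plausible event numbers (about 1 to 3 per variable if all 39 enter) would leave it overfitted

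*Protocol article*

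**What the plan says.** Under Data handling and statistical analysis, the protocol article names the model: "Multivariate Cox proportional hazards models will be used to assess predictors of new foot ulceration and time to event secondary outcomes". Each risk factor is first fitted one at a time with baseline demographics and possible confounders from Table 9. The retention rule begins: "Confounders will be retained if they change the estimated associations between risk factors and the outcome by 10 % or more"; a confounder is also kept if it is significant at 5%. The next step is: "After a number of iterations, all risk factors will then be combined in a multivariable regression model". Forward selection at P = 0.1 is a sensitivity analysis only.

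Table 9 lists 14 continuous and 25 categorical variables. Its footnote reads: "Potential confounding variables that will be considered in the regression models are boldface". Twenty-two of the 39 are bold, and several of these, such as diabetes and neuropathy, are themselves risk factors of interest.

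Two provisions can add terms. The biomechanical section says: "Peak plantar pressures will be measured at seven regions of the foot". The analysis section says: "Interaction terms will then be included in the regression models if there is evidence of an effect modification from any of these variables".

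On testing, "Statistical significance will be set at the conventional level of" P < 0.05, with no factor ranked above another. The Sample size section bases 430 participants on two single-factor contrasts, a 15-point difference by diabetes and a 10-point difference by neuropathy, with a 20% allowance for loss. The Conclusion says: "we have pre-specified our sample size to ensure clinically and statistically meaningful results".

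**The concern.** The number of events, more than the number of participants, limits how many coefficients a Cox model can estimate. The plan prescribes a model whose size follows from the length of Table 9 and is not tied to the expected events. With very few events per coefficient, maximum partial likelihood estimates move away from the null, Wald intervals become too narrow, and P values become too small.

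The hazard ratios from the combined model are what readers are likely to take as the study's list of risk factors. The article expects its results to inform future intervention trials. Exaggerated or chance associations could send those trials after the wrong factors.

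**Working it through.** **Inputs from the article.** N = 430 with 20% loss, so 430 × 0.80 = 344 evaluable. Follow-up is 12 months. Table 9 has 14 + 25 = 39 variables, 22 of them bold. The only incidence figure (Background) is 210 per 1000 person-years in dialysis patients with diabetes, a 12-month risk of 1 − exp(−0.21) = 18.9%.

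**Assumed input.** The Background calls incidence in the dialysis population uncertain, so 10–20% over 12 months is taken for the mixed cohort.

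**The plan's own figure.** The 430 cannot be reproduced uniquely, because neither reference incidence nor exposure prevalence is stated. It is attainable: neuropathy at 15% versus 5%, 60% exposed, with continuity correction, needs 343 evaluable, and 343/0.80 = 429. That setting implies an overall incidence of 0.6 × 15% + 0.4 × 5% = 11%, and 344 × 0.11 = 38 events.

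**Events per variable (EPV)** = participants × risk ÷ number of terms.

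| Setting | Events | EPV, 39 terms |
|---|---|---|
| 344 at 10% | 34 | 0.9 |
| 344 at 18.9% (diabetic rate applied to everyone) | 65 | 1.7 |
| 430 at 20% | 86 | 2.2 |
| 344 at 34% | 117 | 3.0 |

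If the seven plantar-pressure regions enter separately there are 39 − 1 + 7 = 45 terms, and EPV for 34–86 events is 0.8–1.9. A base model with all 22 confounders plus a non-bold factor has 23 terms: 34/23 = 1.5 to 86/23 = 3.7.

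**Effect of this sparsity.** Ordinary Cox models with all 39 covariates (14 normal, 25 binary, latent correlation 0.2) were simulated with 400 replicates per setting and two-sided Wald tests at 0.05. There was no selection step. The setting was either no true predictor or six with a hazard ratio of 2.0.

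| Participants / events | Type I error per factor, no true predictor | Type I error per factor, six true predictors | Median estimate of HR 2.0 | Log-HR inflation |
|---|---|---|---|---|
| 344 / 35 | 7.7% | 9.1% | 2.38 | 25% |
| 344 / 50 | 7.3% | 8.5% | 2.31 | 21% |
| 344 / 65 | 6.9% | 8.4% | 2.26 | 18% |
| 430 / 85 | 6.3% | 6.9% | 2.19 | 13% |

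At 35 events, 7–9% of fits did not converge. A separate simulation in 344 participants with 35–85 events gave 8–11% type I error per factor and estimates of about 2.2–2.4 for a true hazard ratio of 2.0. With only 8 covariates its results were near nominal. Together the runs span about 6–11% for type I error and roughly 13–27% for log-HR inflation.

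**Number of tests, a separate matter.** For 39 independent, exact tests at 5%, the chance of at least one false positive is 1 − 0.95^39 = 86%, and 39 × 0.05 = 1.95 false positives are expected if every factor is null. The 39-term simulations gave 89–94%, so most of that figure comes from the number of tests and little from overfitting.

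**The case against.** The strongest reply is that the article does not say 39 variables are forced in. The sentence follows a retention rule and refers to repeated iterations, so a retained subset is a plausible reading. That stands, and the simulated figures apply only to the literal all-factor reading. It does not remove the problem: a retained subset would be chosen on the same data that supply its P values, and the base models may already carry up to 22 confounders.

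The event count is also assumed. Recurrent ulcers and re-ulceration of baseline ulcers count as outcomes, and records are searched up to death, so events could be higher than 344 participants at 10% would suggest. This stands too, but even 117 events leave an EPV of 3.

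A predefined analysis plan is to follow. A reader might infer that silence on penalisation, validation or multiplicity is itself a fault. It is not, because an article may leave these to that plan. The criticism is of the model that the article does prescribe.

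A reader might also infer that the plan breaks its own 5% level because some false positive is nearly certain. The documents do not support this: the 5% is a per-test level and family-wise control is never claimed.

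Finally, the one-at-a-time adjusted models are already planned, and diabetes and neuropathy already stand apart in the Sample size section. Much of the remedy therefore exists and needs only to be given priority.

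**Conclusion.** The point holds in this form. The plan prescribes a combined Cox model of all risk factors without tying its size to the events. With 34–86 assumed events, EPV is 0.9–2.2 if all 39 enter, and about 1.5–3.7 for a fully adjusted base model. Fitted by ordinary Cox regression, the all-factor model would give moderately too many false positives per factor (about 6–11% against 5%) and hazard ratios exaggerated by roughly 13–27% on the log scale.

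These sizes rest on the assumed incidence, on assumed covariate distributions and correlation, and on ordinary estimation, which is inferred because only plain Cox models are named. The low EPV does not depend on the exact incidence.

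A reader might go further and conclude that the results would be worthless or that the sample size is wrong. Neither follows. The departures per factor are moderate, and the sample size was set for two single-factor contrasts and makes no claim about the combined model. This should be settled before analysis; data collection is unaffected.

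**What to change.** - Make the one-at-a-time models the inferential analysis, each with a small adjustment set fixed in advance and sized to the expected events.
- Name diabetes and peripheral neuropathy as the primary factors and label all others exploratory.
- For the combined model, choose one of two routes: limit it to a pre-specified number of terms supported by the observed events, or fit it with shrinkage (a penalised Cox model is one option) and internal validation of the whole model-building process.
- Do not interpret unpenalised hazard ratios and P values from an all-factor model.

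The cost is analysis-plan wording and some extra analysis work, with no new participants or data. Smaller adjustment sets may leave residual confounding. If penalisation is used, estimates are shrunken and their intervals are less familiar to readers.

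### Effect modification by diabetes and sex is gated on separately fitted stratum models and an undefined standard of evidence, with no requirement to test the interaction term

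*Protocol article*

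**What the plan says.** All of this stands in the protocol article under Data handling and statistical analysis. The text first says "Possible interactions will also be assessed", without a method. It then fixes a sequence. Step one: "Strata specific analysis of regression models using diabetes (yes/no) and sex (male/female) will be conducted to assess variables for possible effect modification". Step two: "Interaction terms will then be included in the regression models if there is evidence of an effect modification from any of these variables". The general threshold is given as "Statistical significance will be set at the conventional level of" P < 0.05. The section does not say what counts as evidence in step two, such as discordant P-values, a difference between hazard ratios or a formal test. It does not say whether the added term is tested, kept or dropped. It names no list of factors for which effect modification is of interest.

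The same section says that a predefined analysis plan will be agreed with a biostatistician before the analysis. That plan is not at hand.

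**The concern.** The stated order makes the stratum comparison the gate and the product term its consequence. Two models fitted separately each ask whether a factor matters within that stratum. Neither asks whether the two coefficients differ. A factor can have the same effect in both strata and still reach P < 0.05 in one and miss it in the other through sampling variation alone. The gate can also fail the other way: two clearly different hazard ratios, both significant or both non-significant, may raise no flag.

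What is at stake is a statement that some factor predicts ulceration only in people with diabetes, or only in one sex. The study recruits people with and without diabetes and intends its findings to inform later intervention trials, so such a statement could steer who is targeted.

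**Working it through.** **The plan's own figure.** The Sample size section gives "a sample of 430 participants" for 80% power, with a "clinically worthwhile difference of 15 % in the incidence of foot ulceration between those with and without diabetes" and a "clinically worthwhile difference of 10 % in the incidence of foot ulceration between those with and without peripheral neuropathy". The base incidences and group shares are not given, so 430 can be neither confirmed nor refuted. Both targets are main effects; neither concerns an interaction. The figure therefore does not decide this point and serves only to set the number evaluable.

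**Inputs from the document**
- Evaluable: "This sample size also allows for a 20 % loss to follow-up", so 430 × 0.8 = 344.
- Ulcer rate in dialysis patients with diabetes (Background): 210 per 1000 person-years. The 12-month risk is 1 − exp(−0.21) = 0.189, or 0.21 if the rate is read directly as a risk.
- Significance level 0.05, taken as two-sided.

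**Assumptions (not in the document)**
- 50% diabetic, so 172 per stratum.
- Non-diabetic 12-month risk of 0.04–0.09. The lower end is 0.189 − 0.15 = 0.039, which borrows the 15-point target difference. The upper end is a more generous assumed value. Pairing 0.21 with the same 15-point gap gives 0.06.
- A binary factor present in 50% of each stratum.

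**Expected events**
- Diabetic: 172 × 0.189 ≈ 33; 172 × 0.21 ≈ 36.
- Non-diabetic: 172 × 0.039 ≈ 7; 172 × 0.06 ≈ 10; 172 × 0.09 ≈ 15.

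**Power per stratum**, where E is the number of events: Φ(√(0.25 E) × ln HR − 1.96). For E = 33 and HR 2: √8.25 × 0.693 − 1.96 = 0.03, so 51%.

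**Probability of significance in exactly one stratum**, the true HR being the same in both: a(1 − b) + b(1 − a), where a and b are the two powers.

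| Events | HR | a | b | Exactly one |
|---|---|---|---|---|
| 33 v 7 | 2.0 | 0.51 | 0.15 | 0.51 |
| 33 v 7 | 2.5 | 0.75 | 0.23 | 0.64 |
| 33 v 15 | 2.0 | 0.51 | 0.27 | 0.51 |
| 33 v 15 | 2.5 | 0.75 | 0.43 | 0.54 |
| 36 v 10 | 2.0 | 0.55 | 0.19 | 0.53 |
| 36 v 10 | 2.5 | 0.79 | 0.31 | 0.61 |

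The range is 51–64%. The extreme pairing of 36 v 7 at HR 2.5 gives 66%.

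**Other hazard ratios.** In a simulation at 36 v 10 events, discordance was 9.5% at HR 1, 28% at HR 1.5 and about 57% at HR 3. The direct test of the difference in log hazard ratios was significant in 5% at every HR.

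**Is it the unequal event counts?** The same 46 events split 23/23 give power of 0.38 in each stratum at HR 2, so 2 × 0.383 × 0.617 = 47%, against 53% at 36/10. Imbalance adds more at HR 3 (37.5% against 57%), but it is not the source. The mechanism applies equally to the sex strata.

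**If a tested product term follows the screen.** In the same simulation (36 v 10, HR 1 to 3), discordance together with a significant interaction test occurred in 3.4–4.4% of studies per factor.

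**Number of comparisons.** Table 9 lists 39 factors. Against diabetes, 37 remain (diabetes and its duration drop out). Against sex, 38 remain. Diabetes by sex is counted twice, so there are 37 + 38 − 1 = 74 pairs. If all were tested at 0.05, 74 × 0.05 = 3.7 false positives would be expected, under direct tests as well.

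The power formula is a large-sample approximation and is rough with 7–15 events. It shows the order of size only.

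**The case against.** The strongest reply is that the document never says that stratum P-values will be compared. Evidence could mean a formal comparison: the difference between two stratum log hazard ratios divided by its standard error is a legitimate heterogeneity test. The sequence also ends in an interaction term, and if that term is tested at 0.05 the error per factor is no worse than with a direct test. Defining evidence and listing the interactions are matters commonly left to the analysis plan, and effect modification is not a stated aim.

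Most of this stands, and it limits the point. A reader might infer that the plan will necessarily produce false subgroup findings; the text does not support that, since the harm depends on how evidence is judged and whether the term is then tested. A reader might blame few events among people without diabetes. The document gives neither their incidence nor the share with diabetes, and an even split shows nearly the same discordance at HR 2. Nor can the expected 3.7 false positives be charged to the order of steps, because direct tests share them; they argue only for a short list. The text also does not say that every factor in Table 9 will be examined against both modifiers.

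What the reply does not answer is the order itself. The article states a procedure in which separate models decide which terms are added, and it says that terms are included, not that they are tested. A later plan that defined evidence but kept this gate could still let stratum significance decide.

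**Conclusion.** The point holds as a weakness of a stated procedure and should be corrected. Its size is conditional. If stratum significance were the criterion, a common hazard ratio of 2.0–2.5 would look stratum-specific in roughly half to two-thirds of studies, against 5% for a direct test. That rests on 344 evaluable participants, an assumed 50% share with diabetes, assumed non-diabetic risks of 0.04–0.09 and a factor present in half of each stratum. The logical fault needs none of these figures: a difference in significance is not a significant difference, and this is as true for sex as for diabetes.

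**What to change.** Reverse the order. State that effect modification will be assessed by fitting each product term (factor × diabetes, factor × sex) in the whole-cohort model with its adjustment set and testing that term directly. Preferably confine this to a short list of factors named before the analysis. Report stratum-specific hazard ratios with 95% confidence intervals as description, ideally derived from the same joint model. Say explicitly that significance within a stratum will not decide which interactions enter the model or are reported.

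The cost is a change of wording in the analysis plan. No data or participants are added. Fewer interactions may be explored than the present open wording allows.
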